## Abstract

**Background:**

An integrated workplace health promotion program (WHPP) which targets multiple lifestyle factors at different levels (individual and organizational) is potentially more effective than a single component WHPP. The aim of this study is to describe the protocol of a study to tailor a European good practice of such an integral approach to the Dutch context and to evaluate its effectiveness and implementation.

**Methods:**

This study consists of two components. First, the five steps of the Map of Adaptation Process (MAP) will be followed to tailor the Lombardy WHP to the Dutch context. Both the employers and employees will be actively involved in this process. Second, the effectiveness of the integrated Dutch WHPP will be evaluated in a clustered randomized controlled trial (C-RCT) with measurements at baseline, 6 months and 12 months. Clusters will be composed based on working locations or units - dependent on the organization’s structure and randomization within each organization takes place after baseline measurements. Primary outcome will be a combined lifestyle score. Secondary outcomes will be the separate lifestyle behaviors targeted, stress, work-life balance, need for recovery, general health, and well-being. Simultaneously, a process evaluation will be conducted. The study population will consist of employees from multiple organizations in different industry sectors. Organizations in the intervention condition will receive the integrated Dutch WHPP during 12 months, consisting of an implementation plan and a catalogue with activities for multiple lifestyle themes on various domains: 1) screening and support; 2) information and education; 3) adjustments in the social, digital or physical environment; and 4) policy.

**Discussion:**

The MAP approach provides an appropriate framework to systematically adapt an existing WHPP to the Dutch context, involving both employers and employees and retaining the core elements, i.e. the catalogue with evidence-based activities on multiple lifestyle themes and domains enabling an integrated approach. The following process and effect evaluation will contribute to further insight in the actual implementation and effectiveness of the integrated WHP approach.

**Trial registration:**

NTR (trialregister.nl), NL9526. Registered on 3 June 2021.

**Supplementary Information:**

The online version contains supplementary material available at 10.1186/s12889-022-13352-0.

## Background

Non-communicable diseases (NCDs) are the leading cause of death worldwide [1, 2]. Unhealthy lifestyle behaviors are well-known modifiable risk factors of NCDs. Therefore, promotion of a healthy lifestyle is of importance [3, 4]. The workplace is seen as an appropriate setting to promote health including the improvement of a healthy lifestyle [5, 6]. Workplace health promotion programs (WHPPs) can be effective in improving the lifestyle behaviors targeted [7–10]. For instance, a review of reviews by Proper et al. concluded that WHPPs have a positive effect on both body weight-related outcomes and the prevention of mental and musculoskeletal problems [7]. However, it should be acknowledged that in some of these systematic reviews, evidence was limited to moderate [8–10]. Individual participant data meta analyses from Robroek et al. and Coenen et al. even showed that overall there was no statistically significant effect of WHPPs on BMI, physical activity, alcohol consumption, smoking and diet, with the exception of fruit intake [11, 12]. Most interventions included in these reviews focused on the individual or environmental level only. The abovementioned findings indicate that there is a need for new directions in the design of WHPPs [11, 13].

A greater impact on lifestyle and health can be expected from an integrated approach, which targets the individual level as well as the organizational level [14]. Earlier studies have indeed shown greater effects of WHPPs that focus on an environmental component in addition to individually based components on the targeted lifestyle behaviors [8, 15, 16]. Nevertheless, these interventions often include only minimal environmental changes. More extensive environmental changes are necessary [13]. A good example of a successful integrated WHPP is the Lombardy WHP Network, which is recognized as a good practice in the occupational setting in the European Joint Action CHRODIS because of its integrated approach and successful implementation [14, 17]. This program has been implemented in Lombardy, Italy, where participating organizations received a catalogue in which activities on both the individual and organizational level for multiple lifestyle themes are included. Employers chose which activities to implement at both the individual and organizational level. A pilot study with a follow-up of 1 year showed significantly positive effects on smoking cessation and fruit and vegetable intake, and favorable changes were apparent for alcohol intake and physical activity [18]. The Lombardy WHP Network was further successful in the implementation and participation of organizations [19]. Development of the program started in 2011 in Bergamo, and in 2013 it expanded on a regional scale. In 2014, 284 workplaces, employing 139,186 persons, were involved [14, 19]. The catalogue with evidence-based activities was continuously updated, which also contributed to the success of the Lombardy WHP Network [19]. The catalogue may also have played a role in the successful implementation, due to the wide range of small and accessible WHP activities provided, an integrated approach that fits the organization can be composed. Such a WHPP is possibly easier to implement when compared to an imposed extensive WHPP. A similar integrated WHPP, based on the Lombardy WHP Network, has been implemented in Andalusia, Spain [20]. Initial results after a nine-month implementation period showed no statistically significant changes yet, but the frequency of sweets consumption within one organization declined with 6.2% (10.8% vs 4.6%) and physical activity in the same organization increased with 12.3% (23.1% vs 35.4%) [21]. Currently there is a lack of such integrated WHPPs and scientific evidence about their effectiveness and implementation [13].

Because of the integrated approach, successful implementation and effects on lifestyle behaviors, our aim was to describe the protocol of a study to tailor the integrated European good practice Lombardy WHP Network to the Dutch context and to evaluate its effectiveness and implementation by means of a cluster randomized controlled trial. This paper describes two components: 1) the protocol of the systematic tailoring of the Lombardy WHP Network to the Dutch context, and 2) the design of the effect and process evaluation.

## Methods/design

For the first component of this study, the protocol of the systematic tailoring of the Lombardy WHP Network, the Map of Adaptation Process (MAP) will be followed. The MAP is a stepwise and systematic approach for the adaptation of an evidence-based behavioral approach to new contexts [22]. The MAP allows a bottom-up approach, in which stakeholders, such as the employers and employees, will be involved in the different steps [23]. Hence, the program can be tailored to their needs and preferences. The MAP consists of five steps: 1) assessment of relevant lifestyle themes, potential barriers and facilitators for implementation and participation, potential activities to be included in the catalogue and the formulation of criteria for an integrated WHPP in the Dutch context, 2) selection of the final content for the Dutch context adapted catalogue, 3) preparation of the catalogue for implementation, 4) pilot test of the feasibility and comprehensiveness of the implementation plan, and 5) implementation of the program (Fig. 1).

**Fig. 1 Fig1:**
[figure not shown]
Steps from the map of adaptation process

### Tailoring of the Lombardy WHP network to the Dutch context

#### Step 1. Assess

Based on the Lombardy WHP Network, the Dutch WHPP will consist of a catalogue along with an implementation plan to support successful implementation. For the development of the catalogue, lifestyle themes relevant for both the employers and employees will be established. Also, potential barriers and facilitators for implementation of and participation in WHP activities will be identified, these will be used to develop the implementation plan. The catalogue will consist of effective activities to improve lifestyle, an initial draft for the catalogue content will be comprised. Criteria that organizations must fulfill in order to implement activities according to integrated approach in the Dutch WHPP will be formulated.

To identify the relevant lifestyle themes and the barriers and facilitators for implementation of and participation in WHPPs, focus groups with employers and peer-to-peer interviews with employees will be conducted. Focus group will be carried out with managers, HR professionals and prevention workers, whom in this study represent the employers’ perspective. A variety of organizations with both blue collar and white collar employees will be represented in these focus groups. In addition, peer-to-peer interviews, in which employees interview their co-workers will be conducted. Peer-interviewers will be recruited within different organizations and departments, to ensure they represent various job types and educational levels. Peer-to-peer interviewing is a method derived from citizen science, in which participants actively take part in conducting research [24]. Advantages are an efficient data collection and less socially desirable answers as persons are considered to respond more genuinely to their peers [24–26].

A toolkit with WHP activities, developed in 2020 within the Joint Action CHRODIS PLUS [27], will be used as a starting point for the initial draft of the catalogue content together with results from the focus groups and peer-to-peer interviews. The WHP activities will be tailored to the Dutch context.

The criteria of the integrated approach in the Dutch context will be formulated by the researchers based on the definition for an integrated approach of the Lombardy WHP Network and the definition of other Dutch integrated health promotion programs developed by the National Institute of Public Health and the Environment, Center of Healthy Living [28, 29]. Within these integrated programs the individual level and organizational level are further specified into four domains. The individual level is subdivided into two domains, i.e. 1): screening and support, where identification of lifestyle related issues and support in addressing these issues is key and 2) information and education, which focuses on creating awareness about the importance of a healthy lifestyle. The organizational level also consists of two domains: 3) adjustments in the social, digital or physical environment to support a healthy lifestyle and 4) policy adjustments to facilitate and encourage a healthy lifestyle. The present study will follow this definition for an integrated approach (Fig. 2). This definition will also be used to formulate the criteria for the integrated approach.

**Fig. 2 Fig2:**
[figure not shown]
Model of the integrated approach

#### Step 2. Select

The aim of the second MAP step is to discuss the lifestyle themes, derived from the focus groups and interviews in step 1, to be included in the catalogue and the criteria of the integrated approach. This will be done with an advisory board, during a group meeting. The advisory board exists of representatives of employees, employers, the Ministry of Health, Welfare and Sport, and the Ministry of Social Affairs and Employment, as well as experts from the Center for Healthy Living and National Institute for Public Health and the Environment. If necessary, themes will be renamed or reclassified, and criteria will be adjusted. With this information, the initial draft of the catalogue will be adapted.

#### Step 3. Prepare

During the preparation step the catalogue will be finalized and a cluster randomized controlled trial (C-RCT) will be prepared. In doing so, the catalogue will be pre-tested by a working group of managers and supervisors from an organization that is experienced in implementing WHP activities. This is also one of the organizations that will participate in a focus group. The working group will verify the fit of the materials to the organization and staff and they will be asked to critically review the materials and provide feedback on attractiveness, readability and understanding of the instructions. In doing so, the working group will jointly fill in a checklist. If necessary, one representative of the working group will elaborate on this completed checklist during a conversation with the researcher. Information from the checklist and conversation will be used to make changes to the materials and to finalize the catalogue. In preparation for the C-RCT, HR professionals, management, prevention workers and employees from each organization that will participate in the C-RCT will form a practice group which will review recruitment materials, promotion materials and presentations. The practice group will also support in the recruitment of workers to participate in the C-RCT by providing information and creating support among employees.

#### Step 4. Pilot

The implementation plan describes the key elements for implementation of WHP activities and describes necessary resources and relevant persons within the organization that should be involved in the implementation. A pilot-test will be conducted by the working group that also was involved in step 3, to assess the feasibility and comprehensiveness of the draft implementation plan. The working group will be asked to select one activity from the catalogue to apply the implementation plan to. The working group will go through all steps of the implementation plan as if they are implementing the activity. However, the activity will not actually be implemented. The working group will express their views on the comprehensiveness and feasibility of all elements of the implementation plan according to a checklist. A representative of the working group and a researcher will discuss the provided feedback based on the completed checklist if necessary. Information retrieved from the checklist and discussion will be used to adjust and finalize the implementation plan.

#### Step 5. Implement

Several organizations will participate in the C-RCT to evaluate the Dutch WHPP. As part of the evaluation, the program will initially only be implemented in a randomly selected half of the participating departments or locations, depending on the structure of the organization. The remaining participating departments or locations will serve as a waiting list control condition and will receive the WHPP once the trial has ended.

### Evaluation plan

For the second component of this study, the design of the effect and process evaluation will be described.

#### Study population

Dutch organizations will be recruited via the extensive network of the project team members, co-workers and branch specific networks. Inclusion criteria for participants will be: working within the participating organizations for at least 12 hours per week with a contract until the final measurement, including employees with a flexible contract or self-employed persons, who have a contract with the organization for 12 or more hours per week. Exclusion criteria will be: being on sick leave for more than 4 weeks or pregnancy.

#### Recruitment

To recruit and inform employees, different communication channels, such as intranet, newsletters, posters, videos and flyers, will be used. Workers within the participating organizations are invited for an information session, which will be either at the workplace or online. The practice group will distribute an information letter and recruitment materials among the employees approximately 4 weeks prior to the start of the C-RCT. Additionally, the practice group will distribute a link by mail or through newsletters, among their employees, so that employees can obtain more information and/or express their interest in the study to the researchers prior to the information session. Employees who expressed their interest will receive information, an eligibility checklist and informed consent by post (additional file 1). During the information sessions, researchers will explain the study purpose and design. At the end of the session, employees can ask questions to the researchers. Again, the link which employees can use to express their interest in the study will be distributed. Employees can send the signed informed consent and completed eligibility checklist prior or after the information session by post to the researchers, with a return envelope that they receive together with the informed consent. 2–4 Weeks after the information session the baseline measurement will take place for employees who are eligible and returned a signed informed consent.

#### Effect evaluation

##### Study design

The effectiveness of the Dutch WHPP will be evaluated in a two-armed C-RCT with a follow-up duration of 12 months. Clusters will be composed based on working locations or units - dependent on the organization’s structure -, to reduce contamination between the control condition and intervention condition [30]. Clusters in the intervention condition will receive the WHPP, consisting of the catalogue and implementation plan, and are asked to implement activities following the criteria of the integrated approach. Continuation of already implemented WHPPs in organizations is permitted in both the control condition and intervention condition. The Medical Ethical Committee of the VU University Medical Center (VUmc, Amsterdam, the Netherlands) approved the study protocol (2021.0402). The trial is registered in the Netherlands Trial Register (NTR) under the number NL9526. Important amendments of the protocol will be communicated to all relevant parties, i.e. the Medical Ethical Committee of the VU University Medical Center (for review and approval), participating organizations, trial registry, participants and journals. Furthermore, adverse events will be reported to the Medical Ethical Committee of the VU University Medical Center. Representatives of the department of Quality, Occupational Health and Safety, and Environment of the RIVM and/or representatives of the Ethics Committee may select this project to undergo an audit. Topics of such an audit may be the progress of the study, the planning, potential highlights and/or problems. The results of this study will be disclosed unreservedly and will be presented as articles in scientific (peer-reviewed) journals and presentations at scientific conferences.

##### Randomization and blinding

Randomization within each organization will take place at cluster level and after baseline measurements. Two independent researchers will be involved in the randomization process. The first independent researcher will assign consecutive numbers to all of the clusters within an organization. The second independent researcher will receive this list without being informed about which number corresponds with which cluster. This researcher will use a computer program to randomly assign the numbers to the intervention or control condition [31]. The first independent researcher will receive the list with numbers and their allocation to the intervention or control condition and will link this to the clusters within the organization. Then, the research team of the current study will send the program to the clusters in the intervention condition. However, the researcher involved in the data processing and analyses will be blinded for group allocation, because clusters will be re-coded by an independent researcher prior to analyses.

##### Sample size calculation

The sample size needed for the proposed study was based on finding an effect on the primary outcome, a combined lifestyle score as measured using the Simple Lifestyle Indicator Questionnaire (SLIQ) [32]. The sample size calculation was carried out including cluster correction using an estimated intra-cluster correlation coefficient (ICC) of 0.04 [33]. Based on a mean score of 7.02 (standard deviation of 1.5) on a scale of 0–10, a power of 80%, a two-sided alpha of 0.05 and an estimated number of 6 clusters per condition, 264 participants (132 per group) are needed to statistically demonstrate an effect on lifestyle of 10%. Taking into account a loss to follow-up of 20% after 12 months, a total of 330 employees (2 groups of 165) need to be included.

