##### Data analysis

First, descriptive statistics (means, standard deviations, or frequencies) at baseline will be performed for all relevant variables. The effect of the Dutch WHPP on the primary and secondary outcomes will be determined by performing longitudinal linear mixed models, adjusting for baseline differences of the outcome measure. Differences in the primary and secondary outcomes at 6 and 12 months between the WHPP condition and the control condition will be analyzed. Main analyses will be performed following the intention-to-treat principle including all available data of the participants regardless their compliance to the program.

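### The 264 participants for 80% power rest on normal quantiles; with 12 randomised clusters the same inputs give about 71% for the unadjusted comparison.

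*Protocol article*

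**What the plan says.** The Sample size calculation section of the protocol article sizes the trial on "a combined lifestyle score as measured using the Simple Lifestyle Indicator Questionnaire (SLIQ"). It applies a cluster correction "using an estimated intra-cluster correlation coefficient (ICC) of 0.04". The other inputs are these: "Based on a mean score of 7.02 (standard deviation of 1.5) on a scale of 0–10" and 80% power. With "a two-sided alpha of 0.05 and an estimated number of 6 clusters per condition, 264 participants (132 per group) are needed" to show a 10% effect. Allowing for 20% loss to follow-up raises this to 330.

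Two other sections bear on the figure. Under Study design, "Clusters will be composed based on working locations or units", and no cluster sizes are given. Under Data analysis, outcomes are analysed by "performing longitudinal linear mixed models, adjusting for baseline differences of the outcome measure". The sample size section mentions no small-sample correction, no variation in cluster size and no baseline correlation.

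**The concern.** A design effect inflates the variance of the treatment contrast. It does not change the reference distribution against which the contrast is tested. When whole clusters are randomised and there are only 6 per condition, the between-cluster variance is estimated from very few units. The critical value should then come from a t distribution with about 10 degrees of freedom, which is 2.228, and not from the normal distribution, which gives 1.96. A calculation that uses 1.96 overstates power noticeably at this number of clusters.

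The figure concerns the primary outcome. If the trial finds no clear effect, readers will weigh that result against a stated 20% chance of missing a 10% effect. On the inputs as given, the chance is nearer 28.5%.

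**Working it through.** **Inputs** (all from Sample size calculation): SD 1.5; effect 10% of 7.02 = 0.702 points; ICC 0.04; two-sided alpha 0.05; power 80%; k = 6 clusters per condition; 132 evaluable per group, so m = 132/6 = 22 per cluster.

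**1. Reproduce the stated figure.**
- Unclustered n per group with normal quantiles: 2 × (1.960 + 0.8416)² × 1.5² / 0.702² = 71.67.
- Size of each of 6 equal clusters: m = n(1 − ICC)/(k − n × ICC) = 71.67 × 0.96/(6 − 2.867) = 21.96, rounded up to 22.
- Per group: 6 × 22 = 132; total 264; 264/0.8 = 330. All three match.
- Alternatives do not match: individual-level t quantiles give 138 per group, and a 1.0-point effect gives 48.

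The article names neither normal quantiles nor equal clusters. Both are inferred, because together they return exactly 132.

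**2. Power on the same inputs.**
- Design effect: 1 + 21 × 0.04 = 1.84.
- Standard error: √(2 × 2.25 × 1.84/132) = 0.2505.
- Non-centrality: 0.702/0.2505 = 2.803.
- Normal quantiles: 80.0%.
- t with 2 × (6 − 1) = 10 degrees of freedom, critical value 2.228, non-central t: **71.5%**. A simulation of a t-test on 12 cluster means (40,000 runs) gave 71.7%.
- Difference detectable with 80% power on 10 degrees of freedom: 3.11 × 0.2505 = **0.78 points**, and 0.78/7.02 = 11.1%.

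**3. Unequal cluster sizes.** The article gives no coefficient of variation (CV), so the values here are assumptions. The design effect is 1 + ((1 + CV²) × 22 − 1) × 0.04.

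| Assumed CV | Design effect | Power, 10 df | Detectable at 80% |
|---|---|---|---|
| 0 | 1.84 | 71.5% | 0.78 |
| 0.4 | 1.98 | 68.3% | 0.81 |
| 0.6 | 2.16 | 64.7% | 0.84 |

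**4. Baseline adjustment.** The article gives no baseline correlation r, so these values are also assumptions (equal clusters, 10 degrees of freedom). At the upper end, adjustment removes a fraction r² of the total variance. At the lower end, it removes r² of the within-cluster variance only, so the variance of the contrast is 2 × [0.04 × 2.25/6 + 0.96 × 2.25 × (1 − r²)/132].

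| Assumed r | Within-cluster only | Total variance |
|---|---|---|
| 0.3 | 74% | 75% |
| 0.5 | 77% | 83% |

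Power reaches 80% at about r = 0.45 in the favourable case and about r = 0.6 in the other.

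**5. Type I error, if 1.96 were used.** The two-sided tail probability beyond 1.96 on 10 degrees of freedom is 7.8% (simulation 8.1%).

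**The case against.** The strongest reply is that 71% describes an unadjusted comparison at one time point, which is not the planned analysis. The Data analysis section adjusts for the baseline score, and at a moderate correlation that alone could bring power back to 80%. This stands. A reader might infer from the 71% that the trial as designed is underpowered, and the documents do not support that. They give no baseline correlation, and plausible values lead to either side of 80%. What remains is that the sample size section neither states nor uses such a correlation, so its 80% does not follow from what it does state.

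A second reply is that nothing is miscalculated, since 132 and 330 both reproduce. That is also right. The fault is the choice of reference distribution for 12 clusters.

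A third reply is that degrees-of-freedom methods belong in the analysis plan. The method does, but the 80% is stated in the article, and a later choice of test cannot make it hold for the stated comparison. A small-sample test has 71.5% power there, and a 1.96 test keeps 80% only at a type I error near 8%. A reader might infer that the trial will have an inflated type I error. The article names no test or reference distribution, so that risk is conditional.

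Unequal cluster sizes should not be read as a cause of the 71% either. That figure keeps all clusters equal. Imbalance is likely with existing locations or units, but its extent is not documented.

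Finally, 6 clusters per condition is itself an estimate, and randomisation takes place within organisations, so 10 degrees of freedom is approximate. Modelling organisation could cost some: at 8 degrees of freedom, with no variance gain credited, power is 69.1%. More clusters would help: the same 132 per group in 8 clusters gives 79%.

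**Conclusion.** The point holds for the calculation as stated. With SD 1.5, ICC 0.04, 6 equal clusters of 22 per condition and about 10 degrees of freedom, power for a 0.70-point difference is about 71% against the stated 80%. The difference detectable with 80% power is about 0.78 points (11%) against 0.70 (10%). This rests on reading 10% as 10% of 7.02, a reading that reproduces the stated sample size, and on an unadjusted contrast between cluster means.

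The power of the planned baseline-adjusted model cannot be fixed from the article. It could be below or above 80%, depending on the baseline correlation and on cluster-size variation. This should be corrected, but it does not invalidate the design or call for more participants.

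**What to change.** Rewrite the sample size paragraph in one of two ways:

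- State that, with 6 clusters per condition, ICC 0.04 and 132 evaluable participants per group, the unadjusted comparison has about 71% power for a 0.70-point difference (detectable difference 0.78 points at 80% power).
- Or state the power of the planned baseline-adjusted model on about 10 degrees of freedom, giving the assumed baseline correlation and cluster-size coefficient of variation. This option is closer to the analysis that will be run.

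In either case, add one sentence saying that the primary contrast will be tested with matching small-sample degrees of freedom (Kenward-Roger or Satterthwaite), so that a 1.96 Wald test is ruled out.

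The cost is a revised paragraph and that sentence. The stated figure becomes less favourable, or explicitly dependent on an assumed correlation. No extra participants are needed.
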